## Abstract

**Background:**

Physiotherapy is essential for the successful rehabilitation of common shoulder injuries and following shoulder surgery. Patients may receive some training and supervision for shoulder physiotherapy through private pay or private insurance, but they are typically responsible for performing most of their physiotherapy independently at home. It is unknown how often patients perform their home exercises and if these exercises are performed correctly without supervision. There are no established tools for measuring this. It is, therefore, unclear if the full benefit of shoulder physiotherapy treatments is being realized.

**Objective:**

The proposed research will (1) validate a smartwatch and machine learning (ML) approach for evaluating adherence to shoulder exercise participation and technique in a clinical patient population with rotator cuff pathology; (2) quantify the rate of home physiotherapy adherence, determine the effects of adherence on recovery, and identify barriers to successful adherence; and (3) develop and pilot test an ethically conscious adherence-driven rehabilitation program that individualizes patient care based on their capacity to effectively participate in their home physiotherapy.

**Methods:**

This research will be conducted in 2 phases. The first phase is a prospective longitudinal cohort study, involving 120 patients undergoing physiotherapy for rotator cuff pathology. Patients will be issued a smartwatch that will record 9-axis inertial sensor data while they perform physiotherapy exercises both in the clinic and in the home setting. The data collected in the clinic under supervision will be used to train and validate our ML algorithms that classify shoulder physiotherapy exercise. The validated algorithms will then be used to assess home physiotherapy adherence from the inertial data collected at home. Validated outcome measures, including the Disabilities of the Arm, Shoulder, and Hand questionnaire; Numeric Pain Rating Scale; range of motion; shoulder strength; and work status, will be collected pretreatment, monthly through treatment, and at a final follow-up of 12 months. We will then relate improvement in patient outcomes to measured physiotherapy adherence and patient baseline variables in univariate and multivariate analyses. The second phase of this research will involve the evaluation of a novel rehabilitation program in a cohort of 20 patients. The program will promote patient physiotherapy engagement via the developed technology and support adherence-driven care decisions.

**Results:**

As of December 2019, 71 patients were screened for enrollment in the noninterventional validation phase of this study; 65 patients met the inclusion and exclusion criteria. Of these, 46 patients consented and 19 declined to participate in the study. Only 2 patients de-enrolled from the study and data collection is ongoing for the remaining 44.

**Conclusions:**

This study will provide new and important insights into shoulder physiotherapy adherence, the relationship between adherence and recovery, barriers to better adherence, and methods for addressing them.

**International Registered Report Identifier (IRRID):**

DERR1-10.2196/17841

## Introduction

### Overview

Rotator cuff pathology is the most common cause of shoulder pain and disability [1,2], and it is associated with significant utilization of health care resources [3] and societal and economic costs [1]. Exercise-based physiotherapy is the established first-line treatment for this condition [4-6] and is also a critical element of rehabilitation following rotator cuff surgery [7,8]. Adherence to prescribed physiotherapy is essential for successful rehabilitation in both conservatively and operatively managed patients [9,10]. However, adherence to physiotherapy is often poor [9,11], particularly in the home setting [9,12,13] and in worker populations [10]. Currently, there are no established methods to effectively and objectively measure adherence to home shoulder physiotherapy [12,14]. Thus, the rate and quality of participation with home shoulder therapy and the relationship between adherence and recovery are unknown.

We have developed the Smart Physiotherapy Activity Recognition System (SPARS), a novel solution for measuring adherence to home shoulder physiotherapy from inertial sensor data recorded on a smart watch using state-of-the-art machine learning (ML) techniques [15]. SPARS was shown to classify exercises for participation monitoring with high (99.99%) accuracy in 20 healthy adults.

The proposed study will further develop and validate our technology to assess home shoulder physiotherapy adherence to both participation and technique in a population with rotator cuff pathology. We will measure the rate of adherence, establish the relationship between adherence and recovery, and explore possible patient factors predictive of poor home physiotherapy adherence. In addition, we will examine ethical and related policy issues associated with the deployment of this technology, specifically investigating patient privacy, individual rights, clinical decision making, health resource allocation, and policy in the setting of artificial intelligence–based surveillance of patient self-management strategies. Guided by ethical analysis and a user-centered design process, we will develop and pilot test a conscientious rehabilitation program with individualized adherence-driven patient care.

### Rotator Cuff Pathology

Shoulder pain and dysfunction are among the most common musculoskeletal health problems and can affect 16% to 21% of the adult population with increasing incidence in advancing age [16-18]. Shoulder pain and dysfunction have an impact on the performance of essential activities of daily living (eg, dressing, hygiene, eating, and work) and result in substantial utilization of health care resources [3]. Rotator cuff pathology is the most common cause of shoulder pain and disability [1,2], accounting for up to 60% of all shoulder conditions [19]. Rotator cuff pathology is also a common cause of disability and employee time loss in the workplace and is associated with a high rate of claims and large societal and economic costs [1]. In the Ontario worker population, the shoulder is the second most frequent site of injury (after lower back) for high-impact claims [20].

Physiotherapy and nonnarcotic analgesia are the first-line treatment for symptomatic rotator cuff pathology [21]. Numerous studies and systematic reviews have concluded that many patients undergoing nonoperative rehabilitation for rotator cuff pathology achieve significant and durable improvements in shoulder pain and function [4,5,19,22-33]. The effectiveness of rehabilitation depends on the physiotherapy protocol that is used. Holmgren et al [34] demonstrated that a specific exercise protocol supervised by physiotherapists was superior to a self-directed range of motion exercises performed at home. Østerås et al [35] demonstrated a dose-response to rotator cuff rehabilitation, with high-dose (greater frequency and intensity) exercise training producing greater benefits than low-dose training.

Clinical trials have not demonstrated a clear benefit of surgical intervention over physiotherapy for the initial treatment of degenerative rotator cuff tears [22,23,36-38]. Current clinical practice guidelines, therefore, recommend that surgical management of rotator cuff pathology should be reserved for some selected cases (acute full-thickness traumatic tears in young patients) and when nonoperative modalities have failed to achieve the desired improvement in the function or symptoms after 6 to 12 weeks [24,39]. Postoperative rehabilitation with exercise-based physiotherapy is considered an essential component in the surgical management of rotator cuff pathology [7,8].

### Home Physiotherapy for Rotator Cuff Pathology

There is little comparative data on the relative effectiveness of supervised physiotherapy versus home-based exercise for rotator cuff pathology [3,24]. Although several trials have sought to address this question [34,40-42], all were of low sample size and adherence to the prescribed physiotherapy was not measured. The efficacy (or lack thereof) of a self-management strategy can only be determined if it is adhered to, which requires measurement of adherence. These studies also used different exercise regimens for their study groups, with the group in supervised therapy receiving a more extensive, specific, and individualized exercise regimen. To our knowledge, no study has directly compared the supervised and independent performance of the same rotator cuff rehabilitation protocol or sought to determine the optimal balance between supervised and independent exercise in hybrid programs. Despite these limitations, the efficacy of independent exercise for rotator cuff rehabilitation is supported by many studies with good outcomes that made extensive use of home exercise in their rehabilitation protocol [3,7,8].

### Adherence to Rehabilitation

Adherence is defined as the extent to which the patient follows medical instructions [43]. There is a general assumption that, where a treatment program is efficacious, adherence to the program improves outcome. Patient adherence to a prescribed physiotherapy has been shown to be an important predictor for the successful management of musculoskeletal disorders [9]. However, adherence to standard exercise protocols is often poor with estimates of non or partial nonadherence varying between 50% and 70% [9,11], with worse adherence for home exercise protocols [9].

In the context of physiotherapy and rehabilitation, the concept of adherence is multidimensional [44]. It includes behaviors such as attending clinical appointments, actively participating in physiotherapist-supervised rehabilitation activities, carrying out home exercise and rehabilitation activities, avoiding potentially harmful and contraindicated activities, and wearing protective or therapeutic devices [44]. Physiotherapy clinic attendance is readily measured, and the Sport Injury Rehabilitation Adherence Scale [44] has been used for evaluating in-clinic adherence. The correct use of protective devices has been measured by observations at clinical follow-up [10] and with temperature sensors [45-47].

Measuring adherence to home physiotherapy exercises remains an open problem [48]. Adherence to this component of a rehabilitation program is particularly vital as this activity calls for the greatest level of independent patient engagement in the rehabilitation process. Adherence diaries, in which patients log their independent exercises, is the recommended and most widely used measure of adherence to home exercise [48]. However, adherence diaries have significant limitations. The validity and reliability of the adherence diary have not been established, and poor patient acceptability results in low rates of diary completion [48]. Furthermore, the written diary has no means to establish if the prescribed exercises have been performed correctly. The proposed study will validate a novel method for measuring participation and technique adherence to home shoulder physiotherapy exercises.

### Adherence to Rotator Cuff Rehabilitation

Several studies on patients with rotator cuff pathology have measured rehabilitation adherence variables, including clinic attendance, adherence to postoperative restrictions, and home physiotherapy participation during rotator cuff rehabilitation [4,10,13,26,49-51]. Nonadherence (eg, to protective device use and clinic attendance) is more prevalent in workers’ compensation patients (52%) than nonworkers (4%) [10]. There is also a relationship between adherence and improved clinical outcomes in the nonoperative [50] and operative management [10,51] of rotator cuff pathology.

Unfortunately, adherence to home rotator cuff exercises has only been measured with adherence diaries [4,26,50] or in response to directed questioning [51]. The completion rates for the adherence diaries varied from 60% to 75% [4,26,50]. Furthermore, the validity of a patient’s self-reported adherence is questionable as a research instrument [52]. Therefore, the rate and effect of adherence to home rotator cuff exercise participation and technique remain unknown. The proposed study will address this knowledge gap in a cohort of 120 patients with rotator cuff pathology.

### Are Home Shoulder Physiotherapy Exercises Performed Correctly?

Patients with rotator cuff pathology have abnormal shoulder kinematics [53,54]. Due to the weakness of the rotator cuff, these patients develop a functional instability, where shoulder motion reduces the available supraspinatus muscle outlet, causing impingement [55]. There is a known relationship between altered shoulder kinematics, pain, and rotator cuff tear size [56]. It is believed that the altered kinematics and impingement exacerbate the condition, contributing to ongoing deterioration of the rotator cuff [54,55]. Restoration of normal shoulder kinematics, in particular muscular control of the scapula, is a focus of physiotherapy for rotator cuff pathology [19,57], and there are some data that contribute to improved patient outcomes [58]. An important role of the physiotherapist in rotator cuff rehabilitation is to supervise the process of kinematic retraining, ensuring that appropriate muscle recruitment and motion patterns are developed and maintained during exercise [59]. No study has determined whether the motion patterns trained during supervised therapy sessions are maintained in the home setting or independent exercise. The proposed study seeks to establish if there are kinematic differences between supervised and home rotator cuff rehabilitation exercises and determine if there is a relationship between exercise technique and shoulder recovery.

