##### Hypotheses

The related hypotheses are as follows:

Exercise technique adherence is better for supervised sessions than at home (*P*<.05).There will be a statistically significant association (*P*<.05) between home physiotherapy exercise participation and technique adherence and the identified clinical outcomes.

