### Data Analysis

#### Sample Size

The proposed sample size of 120 for clinical validation yields a power of 80% to detect weak correlations (*R*>0.25) between physiotherapy adherence and clinical outcomes, accepting a 5% alpha error. Sample size feasibility was confirmed by the WCP, anticipating a recruitment rate of 70%. The pilot study sample size (20) was used to detect implementation challenges with an incidence rate greater than 15% at a 95% confidence level [124] (not statistically significant differences in clinical or economic outcomes).

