#### Criterion Validity

Changes in clinical outcomes will be evaluated as a function of SPARS adherence measures using univariate linear regression analysis, with management subgroup (conservative or operative) and population subgroup (worker or patient) as moderators. This analysis will examine both the concurrent and predictive effects of home physiotherapy adherence on clinical outcomes.

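### The specified outcome regressions are univariate, so a technique–recovery association may partly reflect amount of exercise; a mutually adjusted model should be added and squared with the abstract

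*Protocol article*

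**What the plan says.** Four places in the protocol article bear on this.

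- **The question.** The introduction (Are Home Shoulder Physiotherapy Exercises Performed Correctly?) intends to "determine if there is a relationship between exercise technique and shoulder recovery". The Aim 2 Hypotheses expect a statistically significant association "between home physiotherapy exercise participation and technique adherence and the identified clinical outcomes".
- **The outcome model.** Criterion Validity states: "Changes in clinical outcomes will be evaluated as a function of SPARS adherence measures using univariate linear regression analysis". The only further terms it names are two patient subgroups, management (conservative or operative) and population (worker or patient), which enter as moderators.
- **The abstract.** Its Methods paragraph says that the study will "relate improvement in patient outcomes to measured physiotherapy adherence and patient baseline variables in univariate and multivariate analyses".
- **The multivariable model.** The only one in Data Analysis, under Univariable and Multivariable Analyses, has adherence as the dependent variable and baseline factors as predictors. Recovery is not its outcome.

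Participation and technique are separate measures from separate classifiers. Participation is the percentage of prescribed activity in each two-week interval. Technique comes from a second classifier, and the article gives it no patient-level scale or denominator.

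**The concern.** Both measures come from the same patient wearing the same watch. They could be correlated for behavioural reasons, or because of shared tracking error; the Discussion accepts that such error may be biased towards certain subjects. If they are correlated, the technique slope from a model without participation carries part of any participation effect, and the reverse. No outcome model described in Methods separates the two.

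Two readings of the results are at stake. One is any statement that how patients exercise matters over and above how much they do. The other is the Discussion's argument that a positive adherence–recovery relationship would further support the validity of the algorithm. For the technique classifier that support is weaker if its association with recovery could have come from participation alone.

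**Working it through.** **Inputs from the Sample Size section.** N = 120 and 80% power "to detect weak correlations (*R*>0.25) between physiotherapy adherence and clinical outcomes", "accepting a 5% alpha error". Sidedness is not stated.

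**Step 1: reproduce the plan's figure.** Fisher z, two-sided 5%: power = Φ(atanh(0.25) × √117 − 1.96) = Φ(0.2554 × 10.817 − 1.96) = Φ(0.80) = 0.789. The noncentral t for a single regression slope gives 0.801. The stated 80% therefore reproduces as two-sided power for one correlation at a time. One-sided power would be 0.868, which does not match.

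**Step 2: assumptions that the documents do not supply.** Let ρ be the correlation between participation and technique, taken over 0 to 0.7. Let the participation–outcome correlation be 0.25, the plan's own value, and let technique have no direct effect. All 120 patients are taken as complete, with one outcome and no moderators.

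**Step 3: the univariate technique test.** The correlation of technique with outcome is then r = 0.25ρ. The chance of a significant result is Φ(atanh(r)√117 − 1.96) + Φ(−atanh(r)√117 − 1.96). Simulation used 4,000 trials per row.

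| ρ | r = 0.25ρ | Univariate, formula | Univariate, simulated | Adjusted for participation, simulated |
|---|---|---|---|---|
| 0 | 0 | 5.0% | 4.8% | 4.6% |
| 0.3 | 0.075 | 12.8% | 12.9% | 4.6% |
| 0.5 | 0.125 | 27.4% | 26.9% | 5.7% |
| 0.7 | 0.175 | 48.1% | 49.5% | 4.7% |

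The univariate rates rise with a stronger participation effect. At a participation–outcome correlation of 0.4, they are about 26%, 59% and 87% for ρ = 0.3, 0.5 and 0.7.

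**Step 4: what the joint model costs.** Suppose both measures have direct standardized effects b = 0.25. Then R² = b²(2 + 2ρ), and the partial correlation of technique is b√(1−ρ²) / √(b²(1−ρ²) + 1 − R²). Power is Φ(atanh(partial) × √116 − 1.96).

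| ρ | Variance inflation 1/(1−ρ²) | Partial correlation | Power for technique |
|---|---|---|---|
| 0 | 1.00 | 0.258 | 0.81 |
| 0.3 | 1.10 | 0.252 | 0.79 |
| 0.5 | 1.33 | 0.234 | 0.73 |
| 0.7 | 1.96 | 0.197 | 0.58 |

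The loss is small at moderate correlation and material only when the two measures nearly duplicate each other.

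**The case against.** The strongest reply is that the article asks only about association, and univariate regression answers that. This stands. In the scenario above, technique truly is correlated with recovery, so detecting it is not a false positive for the Aim 2 hypothesis as worded. It misleads only if read as an effect of technique apart from amount of exercise.

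A second reply is that the abstract announces multivariate outcome analyses and does not exclude entering both measures; a condensed article may also leave the covariates to a fuller document. Strictly, univariate can also mean a single response variable. This stands in part. It would be too strong to say that the study cannot separate the two. But Methods describes no such model, and Criterion Validity and the abstract do not say the same thing.

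A reader might infer three further things that the documents do not support.

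- **That correctly performed exercise is never tested.** No combined measure is named, but technique adherence has no stated denominator and could be computed on the prescribed amount. Nothing in the article promises a combined exposure.
- **That these slopes will decide what the Aim 3 pilot acts on.** Program design is said to draw on qualitative ethical and policy analysis, knowledge translation and user-centred design.
- **That participation and technique are in fact correlated.** This is plausible, but the article gives no figure.

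**Conclusion.** The point holds as a limit on interpretation. The specified outcome model tests each adherence measure's association with recovery. It does not show whether technique matters beyond participation, or participation beyond technique, and the multivariate outcome analysis announced in the abstract has no counterpart in Methods.

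The size depends wholly on an unknown correlation. At zero there is no problem. Across assumed values of 0.3 to 0.7, with the plan's own 0.25 for participation, a technique measure with no effect of its own would be significant in 13% to 48% of trials, where an independent-effect claim should err 5% of the time. The change is worth making because it is cheap; the stated hypothesis is not tested wrongly.

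**What to change.** In Criterion Validity:

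1. Keep the univariate models as the test of association.
2. For each outcome, add one model with participation and technique together, retaining the two moderators, and report each slope adjusted for the other.
3. Base any statement that technique matters beyond amount of exercise, or the reverse, on the adjusted slope.
4. Reconcile the section with the abstract by describing the multivariate outcome analysis there or amending the abstract.

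A correctly performed share of the prescription could be added as an exploratory exposure, but it is not required; it would add tests across the five outcomes.

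No new data are needed. The price is wider intervals when the two measures are strongly correlated, as in the second table. Moderator terms for both measures will add to this, since only 9 of the first 46 recruits had compensation claims.

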### Factors Affecting Adherence

The barriers to adherence to supervised outpatient physiotherapy clinics have been summarized in a systematic review by Jack et al [12] in 2010. There was strong evidence to suggest that low baseline levels of physical activity; low in-treatment adherence to exercise; low self-efficacy, depression, and anxiety; helplessness; poor social support; greater perceived number of barriers to exercise; and increased pain during exercise are all significant barriers to physiotherapy adherence. The majority of studies reviewed measured adherence only in terms of clinic appointments. Several studies [60-64] investigated the barriers to adherence to unsupervised home exercise programs. However, these studies suffered from the limitations of the existing adherence diary instrument outlined previously (poor objectivity, poor compliance with the diary, and inability to measure technique adherence). The barriers to unsupervised home physiotherapy, therefore, remain uncertain; they will be explored in the proposed study.

